### **3.4. End-of-study open-ended interviews with clients**

In the final month of the study, open-ended interviews will be performed with 30 female and 30 male patients recruited from the 18 sites. The purpose of these in-depth interviews will be to obtain qualitative information about their experience undergoing contraceptive counseling and receiving family planning methods at the site and the acceptability of these services. The final version of the interview guide will be submitted to the IRB prior to initiating data collection.

A convenience sample of 30 women and 30 men will be invited to participate in the open-ended interview. This interview will be performed in the respondent's preferred language in a private area of the centre and will take approximately 30 minutes to complete. The inclusion criteria will be:

- 1) HIV-positive woman or man obtaining care at the PSC site
- 2) Not currently pregnant (if woman)
- 3) Age 18 to 45 years old if female; age 18+ if male
- 4) Has not received vasectomy or bitubal ligation
- 5) Willing and able to give informed consent

All interviews will be tape recorded (if the client gives his or her consent), transcribed, translated to English, and a content analysis will be performed using the qualitative software ATLAS.ti. Subjects will be reimbursed a maximum of USD\$3 (approximately 200 Kenyan Shillings at current exchange rate) for transport.

### **Study and data management**

The proposed study will utilize administrative offices at Suba District Hospital and/or Migori District Hospital. The study will maintain space for a desk, computer, and a locking file cabinet. The 18 study sites will be clinics within Suba, Kisumu East, Rongo and Migori District MOH. The study staff will include a study coordinator and a team of local language interviewers/research assistants. The study coordinator, under investigator guidance, will supervise the data collection, assist in intervention design, oversee the intervention implementation, and conduct regular site visits. He or she will also be responsible for data checking, quality control, and overall management of the data. Local language interviewers /research assistants will be responsible for abstraction of data from patient records and for conducting all interviews with clients and providers.

Digital recordings of the open-ended interviews with clients and clinic staff will be uploaded to a computer and transcribed into MS Word files by staff experienced in transcription, who will not have access to any identifying information on the participants. Recording and transcription files will be password-protected. Data from the surveys performed with female clients and clinic staff will be entered into SPSS by a member of the research team. These files will also be password-protected.

### **ENDPOINTS**

**Primary Outcomes** (data abstracted from clinic encounter forms from all HIV-positive clients):

1. Contraceptive prevalence
  - a. Will compare post-intervention data from intervention sites to data collected over same time period from control sites
2. Pregnancy rate (number of pregnancies/number of unique clients seen during post-intervention data collection period) and percent of pregnancies that are unplanned
  - a. Will compare post-intervention data from intervention sites to data collected over same time period from control sites

**Secondary Outcomes** (data collected from KAP surveys and in-depth interviews):

1. Knowledge of contraceptive methods among HIV-positive clients
  - a. Will compare pre-intervention rates from baseline data to post-intervention data at intervention sites

- b. Will compare pre-intervention rates from baseline data to post-intervention data at control sites
  - c. Will compare post-intervention data from intervention sites to data collected over same time period from control sites
- 2. Knowledge of contraceptive methods among providers, including peer counselors, at HIV care and treatment centers
  - a. Will compare pre-intervention rates from baseline data to post-intervention data at intervention sites
  - b. Will compare pre-intervention rates from baseline data to post-intervention data at control sites
  - c. Will compare post-intervention data from intervention sites to data collected over same time period from control sites
- 3. Acceptability of family planning services
  - a. Will compare pre-intervention rates from baseline data to post-intervention data at intervention sites
  - b. Will compare pre-intervention rates from baseline data to post-intervention data at control sites
  - c. Will compare post-intervention data from intervention sites to data collected over same time period from control sites
- 4. Feasibility of providing family planning services at HIV care and treatment centers (data from post-intervention surveys of clinic staff)
- 5. Reproductive intentions of HIV-infected clients receiving care and treatment (data from baseline client surveys and in-depth interviews)

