### **Study population/Study subjects**

The study population will primarily consist of HIV-positive men and non-pregnant, HIV-positive women of reproductive age who obtain care at the FACES-supported PSCs in Suba, Kisumu East, Rongo and Migori Districts in Nyanza Province, Kenya. In addition, study subjects will also include clinic staff at the FACES centers included in the study.

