### **3. Part III: Post-intervention data collection (Months 7-15)**

#### **3.1. Post-intervention site-based data collection**

Over the following nine months, data on contraceptive prevalence, contraceptive methods used and pregnancy (including degree to which pregnancy was planned and desired) will be collected, as part of routine care, at the 18 sites (twelve intervention and six control sites) among women age 18-45 and men age 18 and older. Data will also be collected on whether contraceptive counseling was performed at each clinic visit. This information will be collected in the standardized clinic encounter form from all HIV-positive women and men at the time of each visit to the site. At each of the sites, a random sample of 10-15% of all charts will be reviewed during the post-intervention period to determine if the family planning module of the clinical encounter form is being filled out. A draft of the questions that will be used to collect the site-based data is included in Appendix A.

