## **STATISTICAL/ANALYSIS PLAN**

### **Sample size considerations**

**Data abstracted from clinical encounter forms.** We have used ACLUSTER program to generate the number of PSC pairs (or clusters) that we will need to assess changes in contraceptive prevalence and unintended pregnancy. The first input into this program is the size of each cluster (or the number of eligible subjects available at each PSC site). There are a total of 36 FACES-supported PSC sites in Migori, Rongo, Kisumu East and Suba Districts, which are not all equal in size. The first calculation takes into account how we determine the average number of non-pregnant females of reproductive age that are potentially recruitable at each site. The other main input is the desired effect size we aim to be able to measure. Additional inputs include alpha, power and the Intra-cluster Correlation Coefficient (a measure of how similar we expect the two sites in each paired cluster to be to each other, for which we selected an intermediate value). Based on this we need 18 sites, 12 with the intervention and 6 control to be able to evaluate the integration model we propose as described in more detail below.

For the main cluster-randomized trial, the following data were inputted into the ACLUSTER program to generate an estimated number of clusters needed:

- 1. Number of subjects per cluster or site
  - a. The eligible sample includes all FACES-supported PSCs in Suba, Kisumu East, Rongo and Migori Districts. The enrollment in December 2007 at the 16 FACES-supported sites in Suba District was 10,280, at the four sites in Kisumu was 6,593, at the five sites in Rongo was 1,338, and at the 11 FACES-supported sites in Migori District is 4,882.

- b. Because there are not accurate data about the number of non-pregnant women of reproductive age at these sites, we applied estimates based on observations of client demographics at the FACES site in Kisumu, where 65% of all clients are adult females, 89% of the female population is of reproductive age, and 90% of the reproductive age females are not pregnant.
  - c. Applying these estimates, our eligible sample is approximately 12,023 women at 36 sites, an average of 333 women per site. For the sample size calculation, a conservative estimate of approximately 200 eligible women per site was used to allow for inclusion of smaller sites.
- 2. Effect size on primary outcome.

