  - a. The primary outcome upon which we based our sample size calculation is contraceptive prevalence. According to the 2003 Kenya Demographic and Health Survey, approximately 22% of women in a union in Nyanza Province use a modern contraceptive method. This level of contraceptive prevalence is similar to that seen among clients at the FACES sites. We would like to be able to detect a 8% rise in contraceptive prevalence to 30%.
- 3. Assumptions
  - a. Two-sided alpha of 0.05
  - b. Power of 0.8
  - c. Intra-cluster Correlation Coefficient of 0.01
- 4. Sample size.
  - a. Using these estimates, the needed sample size is approximately 140 women at each of the 18 sites, for a total sample of 2,520 women.
  - b. We plan to initially recruit a similar number, 2,520, of male clients, however our primary outcome for men will be the proportion of male clients who report they or their partner are interested in starting a new FP method after receiving FP counseling during their visit. In order to accurately calculate this sample size, baseline data is needed to estimate the baseline proportion of male clients who would express interest in starting a new FP method. Thus, after the baseline data collection phase a more accurate sample size for male clients will be calculated.

**KAP surveys.** Because the largest sample sizes are required for expected proportions nearer to 0.5 than to 0 or 1, we will take the worst-case scenario and assume that for each individual question on the survey approximately half of the participants will answer correctly. We hypothesize that people in the intervention sites will be more knowledgeable after the intervention at the end of the study, so we would like to test for at least a ten percentage point difference in correct answers among patients in the intervention sites (~60% correct) compared to patients in the comparison sites (~50% correct), as well as a 10% increase in correct answers among patients in the intervention sites compared to the baseline results. For a one-sided test of two proportions using two samples, power of 0.8, and an alpha level of 0.05, the required sample size is 325 patients from the intervention sites and 163 patients from the comparison sites for both men (N=488) and women (N=488).

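### Contraceptive prevalence, the first primary outcome, has no consistent population: the endpoint section includes men, while the sample size rests on women only

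*Protocol*

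**What the plan says.** Places in the protocol that point to both sexes:

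- **Endpoints, Primary Outcomes:** both primary outcomes come from "data abstracted from clinic encounter forms from all HIV-positive clients". No denominator is given for contraceptive prevalence. The pregnancy rate is divided by the number of unique clients seen.
- **Specific Objectives, item 1:** compares contraceptive prevalence among HIV-infected individuals. Item 2, on unintended pregnancy, is worded for women.
- **Section 3.1 (post-intervention site-based data collection):** gathers prevalence data in women aged 18-45 and men aged 18 and over. "This information will be collected in the standardized clinic encounter form from all HIV-positive women and men at the time of each visit".

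Places that point to women only, or to non-pregnant women:

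- **Study population:** "HIV-positive men and non-pregnant, HIV-positive women of reproductive age", introduced by the qualifier primarily.
- **Hypothesis:** the increase in contraceptive use is hypothesised among HIV-infected women.
- **Sample size considerations, item 1:** the pool of eligible women is reduced because "90% of the reproductive age females are not pregnant".
- **Sample size considerations, items 2 to 4:** "approximately 22% of women in a union in Nyanza Province use a modern contraceptive method"; the target is 30%; the result is about 140 women at each of 18 sites, 2,520 in all. Men get their own outcome: "however our primary outcome for men will be the proportion of male clients who report they or their partner are interested" in starting a new method after counselling. Its sample size is to be calculated after baseline.

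**The concern.** The Endpoints section is where an analyst looks for the primary outcome. Followed as written, it gives one prevalence over women and men together. For men the form records condom use, vasectomy and the partner's use of other methods, so the pooled figure would mix two kinds of report. That is not the quantity behind the 22% to 30% contrast, and the 2,520 women were not sized for it. The men's primary outcome in the sample size section is missing from the endpoint list, so the two sections also disagree on which primary outcomes exist.

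A second, smaller gap concerns pregnant women. The encounter-form data must include them, because the pregnancy rate is primary outcome 2. The study population and the count of eligible women are restricted to non-pregnant women. Nothing says whether a woman pregnant at the outcome visit stays in the prevalence denominator.

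What is at stake is the meaning of the primary result, and a choice of denominator that could be made after the data are seen.

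**Working it through.** **Inputs (Sample size considerations):** control 22%, target 30%; "Two-sided alpha of 0.05"; power 0.8; "Intra-cluster Correlation Coefficient of 0.01"; 12 intervention and 6 control sites; 140 women per site; about 200 eligible women per site assumed available; 90% of reproductive-age women not pregnant.

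**1. Who was counted.** Enrolment: 10,280 + 6,593 + 1,338 + 4,882 = 23,093. Then 23,093 × 0.65 × 0.89 × 0.90 = 12,023, the protocol's figure. Men and pregnant women were therefore removed before the cluster size was set.

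**2. The stated sample size.** Without clustering, 22% vs 30% at 2:1 allocation needs 358 control women. The design effect at 140 per site is 1 + 139 × 0.01 = 2.39. So 358 × 2.39 = 856 control women, and 856 / 6 = 142.6 per site. The stated 140 reproduces, on women only.

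Power at 140 per site uses SE² = [p₁(1−p₁)/12 + p₀(1−p₀)/6] × 2.39/140:

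- SE = 0.0281; 0.08 / 0.0281 = 2.85.
- Power is 81.4% (normal, unpooled variance), 79.3% (normal, pooled variance under the null) or 76.3% (t, 16 df).

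**3. Pregnant women counted as non-users.** Two assumptions are needed: recorded use in pregnancy is zero, and 22% and 30% apply to non-pregnant women. With 10% pregnant, 0.22 × 0.9 = 19.8% and 0.30 × 0.9 = 27.0%, a difference of 7.2 points.

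| Case | Women per site | Normal, unpooled | Normal, pooled | t, 16 df |
|---|---|---|---|---|
| 22.0% vs 30.0% | 140 | 81.4% | 79.3% | 76.3% |
| 19.8% vs 27.0% | 140 | 75.8% | 73.3% | 70.5% |
| 19.8% vs 27.0% | 140 / 0.9 = 156 | 77.6% | 75.2% | 72.3% |
| 19.8% vs 27.0% | 200 | 81.1% | 79.0% | 76.1% |

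The loss is about 6 points if the 140 include pregnant women, and about 4 if they come on top of 140 non-pregnant women. At 200 per site power returns to within half a point of the undiluted value at 140. For 5% to 15% pregnant the difference is 7.6 to 6.8 points, with pooled-variance power of 76.4% to 70.0% at 140.

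**4. Men pooled in.** The protocol gives neither men's baseline use nor an effect in men. The illustration below assumes 35% men (the most that the 65% adult-female share allows), the same 22% baseline, the same ICC, and men added to the 140 women: 140 / 0.65 = 215 per site, design effect 3.14. Power is by pooled variance.

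| Effect in men | Pooled contrast | Power |
|---|---|---|
| None | 0.65 × 8 = 5.2 points | 51% |
| Half of women's | 5.2 + 0.35 × 4 = 6.6 points | 70% |
| Same as women's | 8.0 points | 85% |

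The range runs from a large loss to a gain. It shows that the pooled result cannot be predicted from the protocol; it does not estimate a loss.

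**The case against.** The strongest reply is that the words in the Endpoints section name a data source shared by two outcomes. Since one of these is pregnancy, the source has to cover pregnant women, and it does not follow that everyone in it enters the prevalence denominator. On men, the sample size section sizes prevalence on women and gives men another outcome, the Hypothesis speaks of women, and the Data analysis plan refers to percentages based on a large number of women. Exact denominators can also be left to the detailed analysis plan that the protocol promises.

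Much of this stands. It means that pooling is a literal reading and not a declared intention. It does not remove the conflict: objective 1 and section 3.1 attach contraceptive prevalence to both sexes, and the men's primary outcome appears in one section and not in the endpoint list. An analysis plan would have to choose between protocol statements that disagree.

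A reader might go further and infer that the endpoint includes pregnant women by rule, so that the effect is diluted. The documents do not support that. The 22% is for women in a union and is said to be similar to that of FACES clients, with no pregnancy restriction; only the count of eligible women excludes pregnant women. If 22% already includes them, an all-women endpoint matches the design and nothing is lost. Zero use in pregnancy is also an assumption, because condoms are among the methods offered and may be recorded then.

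Nor does it follow that the primary analysis should be confined to women not pregnant at the outcome visit. Pregnancy after randomisation is itself a primary outcome, so that restriction conditions on something the intervention is meant to change.

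**Conclusion.** The concern holds as an inconsistency in the population of primary outcome 1. By sex, the objectives, section 3.1 and the Endpoints section conflict with the sample size section, and the men's primary outcome is missing from the Endpoints section. Taken literally, the endpoint does not test 22% vs 30% in women. The consequence of pooling cannot be sized or signed from the document; the 51% to 85% range rests wholly on assumptions about men.

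The handling of pregnant women is an ambiguity with a small, conditional effect: 0.8 points of contrast and about 4 to 6 points of power at 140 per site, if pregnant women count as non-users and the design rates apply to non-pregnant women. About 200 women per site, the availability the protocol itself assumes, would offset it.

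**What to change.** In the Endpoints section:

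1. Define primary outcome 1 as contraceptive prevalence among HIV-positive women aged 18-45, analysed separately from men, and align Specific objective 1 with it.
2. List the men's primary outcome from the sample size section as its own item, and report men's and partners' method use separately from women's prevalence.
3. Use women, not unique clients, as the denominator of the pregnancy rate; read literally, the present denominator includes men.
4. State in advance how women pregnant at the outcome visit are handled and which version is primary, and report prevalence both in all women and in non-pregnant women. Which should lead is a trade-off. The non-pregnant version matches the study population and the count of eligible women. The all-women version avoids conditioning on a post-randomisation outcome.

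The cost is a few lines of protocol text and one extra table. No new data are needed, since sex is known for every client and pregnancy is already collected at the sites. Fixing the population before outcome data are examined also removes the choice of denominator from the analysis stage.

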## **STUDY DESIGN/METHODOLOGY**

### **Overview**

The study will have three parts. During the first part (3 months), baseline data on contraceptive prevalence and unintended pregnancy will be collected at 18 PSCs that are supported by the FACES program in Suba, Kisumu East, Rongo and Migori Districts. Also during this first part, information about knowledge, attitudes and practices related to family planning will be obtained from patients and from clinicians at the sites. During the second part (3 months), an intervention consisting of integrating family planning services will be designed and implemented at twelve of the 18 FACES-supported PSCs. We aim to utilize a 2:1 integration:control model, with delayed integration so as to gradually expand the integration of FP and HIV services throughout the 18 sites, while maintaining the ability to test hypotheses on the effects of integration on health outcomes. After collecting the baseline data, we plan to stratify the clinics into two categories based on the overall patient volume and differences in the structure of family planning provision, i.e., whether or not there is a specific MCH division providing family planning at the site or not. Randomization of sites will then occur among clinics in each of these strata, with a ratio of two intervention sites (integrated model) to one control site (family planning provided in the standard manner at the site). During the third and last part (9 months), data on contraceptive prevalence and unintended pregnancy will be collected from each of the 18 sites. At the end of part three, information about knowledge, attitudes and practices related to family planning again will be obtained from female patients and from clinicians at the sites. In addition, we will administer questionnaires assessing the acceptability of family planning services to patients, and in addition clinic staff will be answer a questionnaire assessing the feasibility of providing integrated family planning services.

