## **1. Part I: Baseline data collection (Months 1-3)**

### **1.1. Baseline site-based data collection**

During a period of three months, baseline quantitative data on contraceptive prevalence, contraceptive methods used and pregnancy (including degree to which pregnancy was planned and desired) will be collected as part of routine clinical care at the 18 sites in Suba, Kisumu East, Rongo and Migori Districts. This information will be collected in a standardized clinical encounter form from all HIV-positive women age 18-45 at the time of each visit to the site. Data will also be collected on HIV-positive men age 18-45 regarding condom use, vasectomy and partner's use of other methods. A draft of the questions that will be used to collect the site-based data is included in Appendix A.

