### **Data analysis plan**

Analyses of data from the study health facilities, given the randomized cluster design, will mainly be conducted at the cluster (health facility) level. Individual level analyses will take into account

cluster effects. Primary analyses will be based on the “intention to treat” (ITT) principle, with facilities randomized to the intervention group classified as delivering “integrated services” regardless of whether or not individual women actually received integrated services.

Preliminary analyses will be conducted to compute study outcome variables and to summarize characteristics of control and treatment sites to assess the effectiveness of randomization. Initial analyses also will involve inspection of the frequency distributions of variables to identify outlying or unusual values. Following univariate descriptions of the data, bivariate and multivariate associations will be assessed as described below.

Analysis of the primary outcomes, contraceptive prevalence and unintended pregnancy rates, and the secondary outcomes, acceptability of services and knowledge related to contraception, will be based on a comparison of means or proportions between study arms using a weighted t-test that accounts for correlations between individual outcomes within sites. Even though there are only 12 health facilities in the intervention arm and 6 health facilities in the comparison arm, each mean or percentage will be based on a relatively large number of women, and the normal approximation to the binomial distribution can be used. These tests will be evaluated based on a two-sided alternative hypothesis, 80% power, and a 5% type I error rate. The same basic approach will be used for the other primary and secondary outcomes. Results will be summarized as odds ratios for models based on binary responses (e.g. use of contraception or experiencing unintended pregnancy), and mean changes for continuous responses (e.g. score on knowledge test).

As noted above, All open-ended interviews will be tape recorded (if the woman gives informed consent), transcribed, translated to English. A content analysis will be performed using the qualitative software ATLAS.ti in order to describe themes in women’s experiences undergoing contraceptive counseling, receiving family planning methods and in the acceptability of these services.

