## **LIMITATIONS**

### **Potential Design Pitfalls**

Non comparable sites: Government facilities in Suba, Kisumu East, Rongo and Migori Districts provide varying levels of care from basic outpatient dispensaries with minimal staff and facilities and services, to the district hospital with comprehensive diagnostic and treatment services including inpatient and outpatient facilities. Comparisons of facilities offering different levels of care would likely introduce confounding factors into the study outcomes. To avoid this potential confounding influence, we will perform an initial assessment of each of the possible sites and divide them into similar groups according to the number of clients served, the type of facility, the geographical location, and the type of HIV and family planning services currently available on site. We will group the sites into two strata based on this information; six intervention and three

control sites will be selected from each of the two strata. In addition, intra-cluster correlation is factored into our data analysis plan (see above section on statistical/analysis plan).

Non-uniform protocol implementation: We will train all health staff and paramedical staff in the standard operating procedure for each HIV care and treatment clinic, including the standard operating procedures for integration or non-integration of family planning services with HIV care and treatment. However, as in all settings, it is impossible to control for individual staff motivation. Therefore, it is possible that some sites will follow the protocol more stringently than others and that some sites will recruit patients more enthusiastically than others. With a randomized design the potential confounder of staff motivation should be evenly distributed in both the intervention and the control arms, thereby minimizing the problem of confounding influences.

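### The primary analysis of contraceptive prevalence uses neither the site baselines nor the randomisation strata; it is valid, but gives up precision that the trial has already paid for

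*Protocol*

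**What the plan says.** Under Endpoints, each primary outcome has one listed comparison: "Will compare post-intervention data from intervention sites to data collected over same time period from control sites". The client-knowledge, provider-knowledge and acceptability outcomes also list comparisons with baseline; the primary outcomes do not.

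The Data analysis plan says that the analysis "will be based on a comparison of means or proportions between study arms using a weighted t-test", and describes the test as one that allows for within-site correlation. It names no baseline covariate and no stratum term. It mentions multivariate associations and models that yield odds ratios, but describes no adjusted primary model. A more detailed analysis plan is promised for the start of the study.

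On the design side:

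- Overview, for Part I: "baseline data on contraceptive prevalence and unintended pregnancy will be collected at 18 PSCs".
- Section 1.1 repeats that "baseline quantitative data on contraceptive prevalence, contraceptive methods used and pregnancy" will be recorded over three months.
- Overview, on allocation: "Randomization of sites will then occur among clinics in each of these strata", two intervention sites to one control.
- Potential Design Pitfalls: "We will group the sites into two strata based on this information", with six intervention and three control sites taken from each.

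**The concern.** With 18 sites, the variation between sites is a large part of the error. At the protocol's inputs it makes up 59% of the variance of a site's observed prevalence (shown in the working). Two features of this design could remove some of it. Clinics that start high tend to stay high, so a site's own baseline predicts its follow-up value. And if the two strata differ in prevalence, that difference is balanced between arms by design but still sits in the residual variance of a plain t-test.

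A post-only t-test leaves both in the error term. It also offers no correction if, by chance, the six control sites start higher or lower than the twelve intervention sites within their strata, although the trial will have measured exactly that. The stake is efficiency and protection against chance imbalance; validity is not at issue.

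**Working it through.** **Inputs from the protocol** (Sample size considerations): 12 intervention and 6 control sites, 22% against 30%, two-sided alpha 0.05, power 0.8, ICC 0.01, about 140 women per site. **Assumed, because the protocol does not give them:** the correlation *c* between a site's true effects (within stratum) at baseline and follow-up, and the share of between-site variance explained by the strata. Different women are assumed in the two periods; women seen in both would raise the correlation.

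**1. The plan's own figure.** Control women needed before clustering, at 2:1 and mean prevalence 0.26:
n = (1.960 + 0.842)² × 0.26 × 0.74 × 1.5 / 0.08² = 353.9.
With six control sites, m = n(1 − ICC)/(6 − n × ICC) = 353.9 × 0.99/(6 − 3.539) = 142.4 per site. The stated 140 reproduces. At m = 140 the design effect is 1 + 139 × 0.01 = 2.39 and power is 79.3% by the normal approximation. No credit is taken for baseline or strata.

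**2. The stated test on 18 site values.** Variance factor: 0.01 + 0.99/140 = 0.01707, of which 0.01/0.01707 = 59% is between-site.
SE = √[0.01707 × (0.22 × 0.78/6 + 0.30 × 0.70/12)] = √(0.01707 × 0.0461) = 0.0281.
Noncentrality 0.08/0.0281 = 2.85; with 16 df, power is 76.3%.

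**3. Adding stratum and baseline, if strata explain nothing.** The correlation of observed site prevalences is r = 0.586 × c. Residual variance is multiplied by 1 − r². Estimating the slope from 18 sites costs a further factor of about 1 + 1/13 = 1.077, and the df fall to 14.

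| c | r | (1 − r²) × 1.077 | Noncentrality | Power |
|---|---|---|---|---|
| 0.8 | 0.469 | 0.840 | 3.11 | 82.4% |
| 0.5 | 0.293 | 0.984 | 2.87 | 76.2% |
| 0 | 0 | 1.077 | 2.75 | 72.4% |

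Without the slope penalty these would read 85.1%, 79.2% and 75.6%, which is too favourable.

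**4. Simulation** (12,000 replicates, 140 women per site per round, ICC 0.01, 6:3 in each of two strata):

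| Strata share | c | Unadjusted | Stratum | Stratum + baseline |
|---|---|---|---|---|
| 30% | 0.7 | 77.5% | 83.2% | 84.9% |
| 30% | 0.9 | 78.6% | 83.9% | 87.9% |
| 10% | 0.5 | 77.6% | 79.4% | 78.6% |
| 0% | 0.8 | 76.8% | 76.6% | 82.7% |
| 0% | 0.5 | 77.3% | 77.0% | 76.7% |
| 0% | 0 | 76.6% | 76.5% | 73.0% |

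Repeat runs agree to about one point, and the last three rows agree with step 3.

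**5. Type I error of the unstratified test.** It is about 3% if strata explain 30% of between-site variance, 4.4% at 10% and 5.2% at 0%. The adjusted models stay near 5%.

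**The case against.** The strongest reply is that nothing here is wrong. A post-only comparison of randomised sites is unbiased, the sample size reproduces without adjustment, and the promised analysis plan could add covariates. The first two points stand. The third stands in part: the protocol never says that strata or baseline will be ignored, so *unstratified* is read from the absence of any such term. But the protocol does fix the comparison and the test for its primary outcomes, so this is a stated choice that can be improved.

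The second reply is that the gain rests on assumed values. That stands. With modest persistence and uninformative strata there is no gain, and with no information there is a small loss. In the rows with a 30% strata share, most of the gain comes from the stratum term (83.2% of the 84.9% at correlation 0.7).

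A reader might infer more from two places. One is the Potential Design Pitfalls section, which treats differences between types of facility as a source of confounding; it is tempting to conclude that the unadjusted estimate is confounded. It is not. With exactly 6:3 in each stratum, stratum is balanced across arms, so apart from weighting a stratum term corrects the standard error and leaves the estimate alone. Only chance imbalance within strata remains for the baseline term to correct.

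The other is to ask for the same baseline adjustment everywhere. The protocol does not support that. Baseline client surveys are convenience samples of about 28 per sex per site, staff surveys total about 30 to 45, and the unplanned share of pregnancies at each site would rest on a three-month baseline that is likely to hold few pregnancies. Such noisy covariates can cost power.

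**Conclusion.** The point holds for contraceptive prevalence, as a matter of efficiency. The stated test is valid, but it omits two pieces of design information that the trial will hold. The gain from using them is about 7 to 9 points of power with informative strata and strong persistence, and about 6 points from baseline alone at correlation 0.8. It is nil at correlation 0.5 with uninformative strata, and minus 3 to 4 points in the worst case. All of this is at the protocol's ICC of 0.01 and rests on assumed persistence and strata shares.

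Strong persistence is plausible, because the same clinics, with fixed structures and many continuing clients, are observed months apart; the protocol does not establish it. The stated test falls slightly short of the planned 80% at the protocol's own inputs (76.3% by formula, 77% to 79% simulated), so the likely gain is worth having. The documents do not support a claim that the planned result would be biased, confounded or too liberal.

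**What to change.** State the primary analysis of contraceptive prevalence as a site-level weighted linear model of post-intervention prevalence on arm, randomisation stratum and the site's baseline prevalence. An individual-level model with the same terms and a small-sample correction is equivalent, and would supply the odds ratios that the Data analysis plan wants to report. Keep the unadjusted weighted t-test as a sensitivity analysis. Fix this before any follow-up data are examined.

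For the other between-arm site comparisons, include the stratum term, since randomisation was stratified. Do not require adjustment for small or convenience-sample site baselines (client surveys, staff surveys, percentage of pregnancies unplanned).

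Cost: wording only and no new data. The model uses two degrees of freedom (16 to 14) and loses about 3 to 4 points of power if neither stratum nor baseline turns out to be informative.
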